## Abstract

**Introduction:** Internet- and mobile-based interventions (IMIs) and their integration into routine psychotherapy (i.e., blended therapy) can offer a means of complementing psychotherapy in a flexible and resource optimized way.

**Objective:** The present study will evaluate the non-inferiority, cost-effectiveness, and safety of two versions of integrated blended psychotherapy for depression and anxiety compared to standard cognitive behavioral therapy (CBT).

**Methods:** A three-armed multicenter cluster-randomized controlled non-inferiority trial will be conducted comparing two implementations of blended psychotherapy (PSYCHOnlineTHERAPY_fix/flex_) compared to CBT. Seventy-five outpatient psychotherapists with a CBT-license will be randomized in a 1:1:1 ratio. Each of them is asked to include 12 patients on average with depressive or anxiety disorders resulting in a total sample size of *N* = 900. All patients receive up to a maximum of 16 psychotherapy sessions, either as routine CBT or alternating with Online self-help sessions (fix: 8/8; flex: 0–16). Assessments will be conducted at patient study inclusion (pre-treatment) and 6, 12, 18, and 24 weeks and 12 months post-inclusion. The primary outcome is depression and anxiety severity at 18 weeks post-inclusion (post-treatment) using the Patient Health Questionnaire Anxiety and Depression Scale. Secondary outcomes are depression and anxiety remission, treatment response, health-related quality of life, patient satisfaction, working alliance, psychotherapy adherence, and patient safety. Additionally, several potential moderators and mediators including patient characteristics and attitudes toward the interventions will be examined, complemented by ecological day-to-day digital behavior variables via passive smartphone sensing as part of an integrated smart-sensing sub-study. Data-analysis will be performed on an intention-to-treat basis with additional per-protocol analyses. In addition, cost-effectiveness and cost-utility analyses will be conducted from a societal and a public health care perspective. Additionally, qualitative interviews on acceptance, feasibility, and optimization potential will be conducted and analyzed.

**Discussion:** PSYCHOnlineTHERAPY will provide evidence on blended psychotherapy in one of the largest ever conducted psychotherapy trials. If shown to be non-inferior and cost-effective, PSYCHOnlineTHERAPY has the potential to innovate psychotherapy in the near future by extending the ways of conducting psychotherapy. The rigorous health care services approach will facilitate a timely implementation of blended psychotherapy into standard care.

**Trial Registration:** The trial is registered in the German Clinical Trials Register (DRKS00023973; date of registration: December 28th 2020).

## Introduction

The effectiveness of psychotherapy in the treatment of mental disorders has been well-documented (1, 2). However, even in countries with a well-developed health care system, treatment rates are low despite the given demand. In Germany, about 28–63% of people with varying mental disorders in need of treatment remain untreated (3). Psychotherapy as one of the first-line treatments for depressive and anxiety disorders (4–6) is provided for only 10–15% of those who receive treatment (7). One reason for this low utilization rate is the shortage of health insurance covered psychotherapies, documented by waiting times of 3–12 months (3). Other reasons might result from conflicting life tasks and challenges to realize time-consuming psychotherapeutic on-site sessions.

Internet- and mobile-based interventions (IMIs) can provide a means of making evidence-based psychotherapeutic interventions available in a timely manner, thereby contributing to reducing the shortage of care (8, 9). The aim is not only to provide information on possible causes, symptoms, and courses of mental disorders, but also to provide parts or the entire psychotherapeutic process digitally (8). The research on IMIs has so far almost exclusively focused on stand-alone IMIs, i.e., online interventions that are used as an alternative to on-site treatment (8, 9). Numerous clinical trials summarized in several meta-analyses have now shown the effectiveness of IMIs in the treatment of mental disorders (8), particularly well-studied in depressive disorders and anxiety disorders (10, 11). Thereby, guided IMIs for mental and somatic disorders are seemingly as effective as the respective on-site treatments (12). However, the evidence refers to participants who are willing to be treated via IMIs. Studies on the acceptance of IMIs show that this only applies to a small part of the target population regarding both patients (13–16) and therapists (17, 18). In addition, the exclusive remote psychotherapeutic treatment of mental disorders, as is the case with stand-alone IMIs, is largely restricted in Germany by the applicable professional regulations.

Blended psychotherapy, i.e., the combination of online intervention elements with standard psychotherapeutic care, is a rather new field of research (19–22). Recent surveys and qualitative studies amongst psychotherapists indicate that blended therapy approaches would be acceptable considering perceived advantages over conventional psychotherapy, including e.g., bridging distances, flexibility, patient empowerment, and therapist support by standardized materials (17, 18, 23, 24). Acceptance rates are seemingly higher amongst psychotherapists with a background in cognitive behavioral therapy (CBT) compared to other therapeutic backgrounds (17, 18).

From a conceptual point of view, blended therapy approaches can be subdivided into (1) sequential and (2) integrated blended therapy concepts focusing on (a) maximizing the effectiveness of psychotherapy or (b) maximizing the efficiency of psychotherapy (19). Examples for sequential blended therapy concepts are IMIs provided prior to on-site psychotherapy, e.g., during waiting-time (25), or IMIs following on-site psychotherapy, e.g., as inpatient aftercare and relapse prevention (26–28).

Regarding integrated blended therapy, Berger et al. (29) examined whether an Internet-based self-help intervention, when used adjunctive to standard psychotherapy, has an additional effect compared to standard psychotherapy for depression. In this randomized controlled trial, integrated blended therapy was superior over standard psychotherapy (*d* = 0.51; *n* = 98). Similarly, Zwerenz et al. (30) documented an incremental effectiveness (*d* = 0.44; *n* = 229) of an Internet-based self-help program in addition to psychodynamic inpatient psychotherapy for depression compared to inpatient psychotherapy only.

IMIs could also be used to optimize the efficiency of psychotherapy. It has been well-established that therapeutic guidance is an active component of IMIs, however, with a yet to be examined ceiling effect from which onward more therapist time does likely not translate into clinically significant higher therapeutic benefits for the average patient (31, 32). Hence, one possible way of implementing blended therapy is to iteratively provide standard psychotherapy combined with Internet- and mobile based self-help modules, with the assumption of non-inferiority. As such, blended therapy could represent a means of providing psychotherapy to more patients in need, against the background of restricted resources as present in most health care systems around the world.

PSYCHOnlineTHERAPY aims to examine the potential of integrated blended therapy by comparing standard CBT-focused outpatient psychotherapy (CBT_standard_) with two implementation variants of integrated blended therapy, (1) PSYCHOnlineTHERAPY_fix_ as a standardized blended therapy concept combining equal numbers of standard therapy sessions and online intervention modules and (2) PSYCHOnlineTHERAPY_flex_, providing therapists with the means of combining standard therapy with online interventions modules as perceived fitting for the respective therapy process at hand. In more detail, the project aims to examine:

the non-inferiority of PSYCHOnlineTHERAPY_fix/flex_ in comparison to CBT_standard_.the cost-effectiveness of PSYCHOnlineTHERAPY_fix/flex_ in comparison to CBT_standard_.the safety of PSYCHOnlineTHERAPY_fix/flex_ in comparison to CBT_standard_.qualitative and quantitative details of the implementation variants with regard to acceptance, feasibility, barriers, and facilitators to identify optimization potential.moderators and mediators of the therapy success as well as potential risks and side effects.

## Methods

### Study Design

A three-armed multicenter large-scale pragmatic, cluster-randomized controlled trial (cRCT) will be conducted comparing the clinical and cost-effectiveness of two implementations of blended therapy (PSYCHOnlineTHERAPY_fix/flex_) compared to standard CBT (CBT_standard_). Quantitative trial outcomes will be complemented by qualitative interview data on the acceptance, feasibility, and optimization potential of PSYCHOnlineTHERAPY in order to gain in-depth insights in participants' experiences. A smart-sensing sub-study, examining ecological day-to-day digital behavior variables via passive smartphone sensing, aims to provide psychotherapy process insights (33).

This clinical trial has been approved by the ethics committee of the German Psychological Society (DGPs no. [name]) and will be reported in accordance with the Consolidated Standards of Reporting Trials (CONSORT) Statement 2010 and the extensions for reporting pragmatic trials, non-inferiority trials, cluster randomized trials, multi-arm parallel group trials, and trials on psychological interventions (34–39). Qualitative data analyses will be reported following the Consolidated Criteria for Reporting Qualitative Studies (COREQ) checklist (40). Cost-effectiveness analyses will be reported according to Consolidated Health Economic Evaluation Reporting Standards statement [CHEERS; (41)] and the guidelines from the International Society for Pharmacoeconomics and Outcomes Research [ISPOR; (42)]. This trial protocol was created according to SPIRIT guidelines (43). The study has been registered in the German clinical trial register under DRKS00023973.

### Participants and Procedure

#### Cluster Definition

The trial will be conducted in psychotherapy outpatient practices in South-West Germany (Baden-Wuerttemberg) that take part in the PNP (Psychotherapy, Neurology, Psychosomatic, and Psychiatry) selective health care services contract of the health insurance companies AOK Baden-Wuerttemberg and Bosch BKK, managed by MEDIVERBUND AG according to §73c SGB V. This contract defines (amongst others) specific psychotherapy services for patients as outlined below. Clusters are defined by psychotherapy outpatient practices that are run by licensed psychotherapists who are PNP contract partners (i.e., authorized to bill according to the PNP contract; https://www.mediverbund-ag.de/file/4922). Psychotherapists who are not PNP contract partners themselves may participate in the study, if they are employed in a practice owned by a PNP contract partner. More than one therapist per practice is allowed to participate in the study.

Psychotherapists are eligible for inclusion in case of a given informed consent and if they (a) are actively working as a psychological psychotherapist, a medical specialist for psychiatry and psychotherapy or psychosomatic medicine and psychotherapy, another physician working as psychotherapist, or a children and adolescent psychotherapist, (b) are (employed in a practice owned by) a PNP contract partner, (c) hold a CBT license, (d) are available during recruitment and assessment period (self-report regarding no already known time-offs), and (e) are capable of including 12 patients into the study during the recruitment period (18 months; self-report). Enrolment and opening of clusters will take place over the entire recruitment period in order to reach the recruitment target of 900 patients. The recruitment target is a median of 12 patients per participating psychotherapist in order to achieve recruitment of 900 patients.

#### Inclusion and Exclusion Criteria of Patients

Psychotherapy outpatients of enrolled psychotherapists are eligible for inclusion in case of a given informed consent and if they (a) are ≥ 18 years, (b) have a depressive disorder or anxiety disorder diagnosis eligible to be treated under the PNP contract (medical record of an ICD-10 F32/33.1-0.3; F34.1; F40.00/0.01; F40.1; F40.2; F41.0-0.3), (c) have a health insurance contract with AOK Baden-Wuerttemberg or Bosch BKK as part of the PNP contract according to §73c SGB V, (d) complete the baseline assessment (online assessment and telephone-based standardized clinical interview), (e) have Internet-access and an Internet-capable device (self-report), (f) have sufficient knowledge of the German language (therapist rating), (g) have no ICD-10-F2 diagnosis (therapist rating) as IMIs are not well-examined for this patient group yet, and (h) show no clinical reasons for exclusion (psychotherapist rating). Exclusion criteria are kept at a minimum in this effectiveness trial embedded in standard psychotherapeutic outpatient care. Suicidal tendencies are not defined as exclusion criteria and will be therapeutically handled by the treating psychotherapist according to established standards for crises interventions in standard psychotherapeutic care. In case of acute suicidal tendencies psychotherapists might judge patients as not clinically suitable for blended therapy (criterion h). Respective therapist decisions will be recorded weekly.

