### Recruitment

Initial recruitment of psychotherapists started in July 2020 and is expected to be finished in July 2021, supported by MEDIVERBUND AG as well as the collaborating professional associations MEDI Baden-Wuerttemberg e.V., Freie Liste der Psychotherapeuten and Deutsche Psychotherapeutenvereinigung (DPtV). First patient in is expected to be included in January 2021. Psychotherapists taking part in the PNP contract were contacted via e-mail and invited to one of four online information events. Furthermore, psychotherapists can express their study interest at www.psychonlinetherapie.de. After informed consent has been given and inclusion and exclusion criteria confirmed, eligible psychotherapists complete baseline assessment. Psychotherapy outpatient practices are consecutively randomized to one of the three trial arms. Psychotherapists are subsequently invited to a 1-day training, which will be tailored to the respective trial arm (PSYCHOnlineTHERAPY_fix/flex_; CBT_standard_). MEDIVERBUND AG assigns a practice structural feature for billing project-specific blended therapy services in accordance with the PNP contract.

Once psychotherapists are allocated to one of the three trial arms and trained for intervention and study protocol adherence, patient recruitment starts. This is expected to take place from January 2021 until June 2022. The psychotherapists assess if patients are potentially eligible for the trial. If this is the case, patients are informed by their psychotherapists about the possibility to take part in PSYCHOnlineTHERAPY. Interested patients will give their informed consent and schedule an appointment for the telephone-based clinical interview online on a tablet provided for study purposes only in the psychotherapy practice. Patients are then invited for the online baseline assessment and the baseline clinical interview is conducted. Once the baseline assessments have been completed, patients enter the trial and are treated for their condition according to trial arm allocation of their psychotherapist following the intervention rational as described below. Follow up assessments will take place as outlined in the flow chart (Figure 1).

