### Randomization, Allocation, and Masking

Psychotherapist outpatient practices will be consecutively randomly allocated to (a) PSYCHOnlineTHERAPY_fix_, (b) PSYCHOnlineTHERAPY_flex_, or (c) CBT_standard_ and informed about group membership via e-mail. Randomization will take place at a psychotherapist practices level. That means, therapists in joint practices are randomized jointly into one of the three trial arms to avoid trial arm contamination. Randomization will be conducted by an independent researcher who is blind regarding the study conditions. Whereas, blinding of psychotherapists is not possible, data collectors are blinded regarding treatment condition. Treatment condition is only known by the study personnel administering allocated treatments to psychotherapy practices. Randomization will be stratified by the number of therapists per practice (single therapist vs. more than one therapist). Two randomization lists will be generated by using the web-based programme Sealed Envelope (www.sealedenvelope.com). Randomization will happen on an individual level and an allocation ratio of 1:1:1 will be performed. In case of dropouts and if it becomes apparent that more than 75 therapists are needed to reach the sample size of *N* = 900 patients, additional therapists will be randomized.

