#### Control Group—CBT_standard_

Patients enrolled in PSYCHOnlineTHERAPY and allocated to the control group will receive standard psychotherapy as described before, following the obligatory diagnostic process in the first few sessions (Table 1). Thereby, therapy follows standard care without a predefined treatment protocol. Details of the psychotherapy provided will be assessed via therapy documentation sheets in order to provide a *post-hoc* description of standard psychotherapy as provided in standard care.

**Table 1 T1:** PSYCHOnlineTHERAPYfix/flex vs. CBTstandard.

**PSYCHOnlineTHERAPY_**fix**_**	**PSYCHOnlineTHERAPY_**flex**_**	**CBT_**standard**_**
on-site diagnostics, indication for psychotherapy and evaluation of suitability for PSYCHOnlineTHERAPY as well as informed consent		
max. 16 sessions in a fixed order alternating an online-intervention module followed by a standard psychotherapy session	max. 16 online or standard sessions, amount and order of online and standard sessions as defined by their therapists	max. 16 standard psychotherapy sessions
end of PSYCHOnlineTHERAPY (standard PNP-based psychotherapy following the first 16 sessions in case of still existing need of psychotherapy as defined by the therapist)		

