### Potential Problems and Solutions

In order to avoid selection bias, PSYCHOnlineTHERAPY follows strict trial role division with Ulm University as principle investigator, intervention content and IT-solution provider and interface to health care service providers and stakeholders. Evaluation of PSYCHOnlineTHERAPY takes place at University of Erlangen-Nuernberg. Thereby, the University of Erlangen-Nuernberg has established a work flow ensuring that randomization, administration of participants, and outcome assessments (interviews) will be conducted independent of each other. Particularly outcome assessors are kept blind toward trial arm allocation. At the beginning of each telephone interview, patients are asked to keep their trial arm allocation disclosed.

Trial arm contamination might occur in joint practices. Hence, psychotherapists in joint practices are randomized and allocated jointly in the same trial arm condition. Resulting clustering effects will be compensated statistically. Different to cRCTs in general practices patient-level trial arm contamination is rather unlikely, as patients do not switch psychotherapists in due course or during times of absence (e.g., vacation) of their psychotherapists. Patients will be asked whether they already took part in PSYCHOnlineTHERAPY before.

Considering that therapeutic alliance, which depends also on the characteristics of the psychotherapists, is one of the most important variables predicting the outcome of psychotherapy (119, 120), randomizing therapists runs the risk of clinically important baseline imbalance. Cluster size was optimized for the pre-specified non-inferiority margin, however, between trial arm baseline imbalance regarding therapist competency needs to be considered carefully when interpreting the final trial results.

Study and intervention protocol adherence will be improved by structured training courses, regular contacts with study psychotherapists as well as assessed via therapists' documentation of their psychotherapies.

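### Therapists who know their arm select patients under an open criterion explained only by unsuitability for blended therapy, so exclusions can differ by arm

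*Protocol article*

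**What the plan says.** **Order of events.** In the Protocol article, Methods, Randomization, Allocation, and Masking, practices are randomized and "informed about group membership via e-mail". Methods, Recruitment adds training tailored to the arm and then: "Once psychotherapists are allocated to one of the three trial arms and trained for intervention and study protocol adherence, patient recruitment starts".

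**Who selects.** Recruitment continues: "The psychotherapists assess if patients are potentially eligible for the trial". On masking: "Whereas, blinding of psychotherapists is not possible, data collectors are blinded regarding treatment condition". Patients enter the trial only after consent and baseline assessment.

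**The criterion.** Under Inclusion and Exclusion Criteria of Patients, item (h) requires that patients "show no clinical reasons for exclusion (psychotherapist rating"). Suicidal tendencies are expressly not an exclusion criterion. The one example of how (h) may operate is: "In case of acute suicidal tendencies psychotherapists might judge patients as not clinically suitable for blended therapy (criterion h"). Therapists' decisions of this kind are to be recorded weekly.

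**Table 1** (in the control-group section) lists an "evaluation of suitability for PSYCHOnlineTHERAPY as well as informed consent". In the extracted text this row appears to span all three arms.

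**The stated safeguard.** Discussion, Potential Problems and Solutions: "In order to avoid selection bias, PSYCHOnlineTHERAPY follows strict trial role division". The division described there separates randomization, participant administration and outcome interviews, and keeps outcome assessors blind.

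**The concern.** In a cluster trial that recruits after allocation, randomization protects the comparison of practices but not the comparability of the patients who are later enrolled. An arm-neutral entry criterion limits the damage. Here the explanation of (h) asks, in effect, whether the patient suits blended therapy. That question matters to a therapist about to deliver it and is close to irrelevant to one delivering standard CBT.

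Two comparisons are exposed:

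- **Non-inferiority.** Against a margin of 0.24 SD, a small difference in case mix between arms is not negligible.
- **Safety.** Safety is a stated aim, and the listed serious adverse events include suicide, suicide attempt and self-injury needing medical care. Uneven exclusion of acutely suicidal patients bears directly on those counts.

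Intention-to-treat analysis does not help, because patients screened out never enter the analysis set.

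**Working it through.** **1. Do the stated safeguards reach the selection step?**

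| Safeguard | What it does | Reaches the recruiting therapist? |
|---|---|---|
| Blinded data collectors | Protects outcome measurement | No |
| Role division | Separates randomization, administration and interviews | No |
| Weekly recording of decisions | Allows imbalance to be detected | It can detect but not prevent; no use in the analysis is stated |
| Intention-to-treat | Keeps enrolled patients in their arm | No, it acts after entry |

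Criterion (g) is a useful contrast. It is also motivated by online interventions, but it is tied to an ICD-10 F2 diagnosis and so can work alike in every arm. Criterion (h) has no such anchor.

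**2. The plan's own sample size, to obtain a standard error.** Inputs from Sample Size and Power Calculation: margin 0.24 SD, one-sided α = 0.025, power 0.8, ICC 0.01, cluster size 12, 300 per arm.

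- Individually randomized: n = 2 × (1.960 + 0.842)² / 0.24² ≈ 273 per arm.
- Design effect: 1 + (12 − 1) × 0.01 = 1.11.
- Clustered: 273 × 1.11 = 303 per arm, about 25 clusters. The stated 300 reproduces, with power 79.7%.
- Standard error of the T3 standardized difference: √(2 × 1.11 / 300) = 0.086.

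**3. Illustration on the T3 contrast.** The documents give no exclusion share and no prognosis for excluded patients, so these are assumptions. Suppose patients of the kind screened out of a blended arm make up a share p of the control arm, score 1 SD worse at T3 than the rest, and do not differ at T0. The contrast then shifts by s = p × 1 SD in favour of blended therapy. When the true deficit equals the margin, P(non-inferiority declared) = Φ(s / 0.086 − 1.96).

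| Share p | Shift s (SD) | False non-inferiority |
|---|---|---|
| 0 | 0 | 2.5% |
| 1% | 0.01 | 3.3% |
| 2% | 0.02 | 4.2% |
| 5% | 0.05 | 8.4% |
| 10% | 0.10 | 21% |

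A second set of assumptions gives a similar picture. If the worst-prognosis 2%, 5% or 10% are excluded in a blended arm only, and the prognostic index correlates 0.3 to 0.7 with T3 PHQ-ADS, the T3 shifts are 0.015–0.035, 0.03–0.08 and 0.06–0.14 SD. False non-inferiority is then about 4–6%, 6–14% and 10–36%.

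**4. The focal test is not a T3-only contrast.** Clinical Analyses bases non-inferiority on the time-by-group interaction over T0 to T3. On a simple change scale the bias is roughly p × (d3 − d0), where d3 and d0 are the excess scores of the excluded patients at T3 and T0.

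- d3 = 1, d0 = 0, p = 5%: 0.05 × (1 − 0) = 0.05 SD towards non-inferiority.
- d3 = 1, d0 = 1, p = 5%: 0.05 × (1 − 1) = 0.
- d3 < d0: the bias runs against non-inferiority. If exclusion follows baseline severity alone, with 5% excluded, a T0–T3 correlation of 0.3 to 0.7 and equal SDs, regression to the mean gives about 0.03–0.08 SD in that direction.

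The figures in step 3 therefore belong to the T3 contrast and carry over to change only when d0 is about zero.

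**The case against.** A reader might infer that harder cases are removed from the blended arms only, and that this biases the trial towards non-inferiority. The documents support neither inference.

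- **Blended arms only.** The wording of (h) names no arm; blended therapy appears only in the explanatory sentence. The Table 1 suitability step appears common to all arms, and PSYCHOnlineTHERAPY there may simply be the name of the trial, since the control-group text also describes control patients as enrolled in it. This stands as far as it goes: (h) formally applies everywhere. It does not settle the matter, because nothing tells a control-arm therapist to judge suitability as if the patient were to receive blended therapy.
- **Known direction.** For the T3 score, bias favours non-inferiority if the excluded patients would have done worse at T3. For the slope it can vanish or reverse, as shown in the working. This objection stands in full.
- **Size.** The article keeps exclusions to a minimum, and its example concerns acute cases that therapists might exclude, so the share could be 1% or 2%, with little effect. The flexible arm allows 0 to 16 online sessions, so the incentive to exclude may be weaker there. Both points stand.
- **Selection-bias statement.** The Discussion gives avoiding selection bias as the purpose of role division, does not claim that all such bias is removed, and warns about imbalance in therapist competency. The fair criticism is narrower: therapists' selection of patients is not named.
- **Unavoidable in this design.** Therapists cannot be blinded. That is true, and it is the reason to make the entry criterion neutral between arms.

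**Conclusion.** The point holds as a risk of differential exclusion, not as a demonstrated bias of known sign. What the text establishes is selection after allocation, by recruiters who know their arm, under an open rating whose only example concerns a treatment the control arm does not get, with no stated safeguard that prevents uneven use.

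The size is scenario-dependent. False non-inferiority of 3.3% to 21% against a nominal 2.5% rests on an assumed excluded share of 1% to 10%, a 1 SD excess at T3, no difference at T0, and the T3 contrast with standard error 0.086. For the focal slope the sign is open. The safety comparison is exposed whichever way the slope bias runs. The sample size itself is not in question. This is a cheap improvement that should be made.

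**What to change.** 1. **Criterion (h).** Word it and its explanatory sentence neutrally between arms: the same question, the same recording and the same consequence for entry in all three. Add an instruction to the control-arm training. Which patients the criterion covers remains the sponsor's clinical decision.
2. **Use the records.** Compare exclusion rates and reasons by arm from the weekly records, and compare T0 severity of enrolled patients by arm.
3. **Sensitivity analysis.** Run a baseline-adjusted T3 comparison as a sensitivity analysis only. T0 PHQ-ADS is already a response in the primary three-level model, so it should not simply be added there as a covariate. Adjustment does not remove selection on unmeasured prognosis.
4. **Discussion.** State under Potential Problems and Solutions that role division does not cover therapists' selection of patients.

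**Cost:** rewording one criterion and the recruitment form, a short training instruction, and a few descriptive tables. A few control patients may be excluded who would otherwise have entered. Unblinded therapists still choose whom to invite, so some selection risk remains and should be acknowledged.
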